**Figure 2 F2:**
[figure not shown]
Study design and timeline.

**Table 1 T1:** Participants by Tier and support level

		**Consultation**	**Consultation plus coaching**	**Total**
**Tier 1**				
	Students	1,950	1,950	3,900
	Leadership team members	24	24	48
	School staff	90	90	180
**Tier 2**				
	Students	153	153	306
	Counselors	6	6	12
	Intervention groups	42	42	84

### Participants

Tier 1 research activities will include 48 teachers, administrators and parents in the leadership teams, 180 school staff for the assessment of school climate, and approximately 3,900 students. Participants in Tier 2 will be 12 counselors and approximately 306 evaluable children who have, or are at risk for, externalizing or anxiety disorders. School personnel will provide all services. Information pertaining to each school will be considered nested within school ‘cluster’ and will be defined as such in the statistical analyses.

### Inclusion criteria

All children will participate in Tier 1. Children in grades 4–8, who meet screening and diagnostic criteria will be included in Tier 2. The screening criterion is a score ≥1 SD on the Conduct Problems or Emotional Symptoms scales of the Strengths and Difficulties Questionnaire (SDQ), a widely-used screening instrument [78], filled out by a teacher. Children meeting screening criterion will undergo a diagnostic evaluation. Children meeting primary diagnosis of ODD, CD, GAD, SAD, or SP (based on a parent structured interview [79] and a symptom severity scale [80] filled out by an independent rater) at Intermediate or Positive level will be eligible for participation. Children with comorbid (secondary) conditions will be included.

### Exclusion criteria

There are no exclusion criteria for Tier 1. Children with a Special Education classification of Intellectual Disability, as well as those who are not able to communicate in English, do not have a principal diagnosis of ODD, CD, SAD, GAD or SP or are not at risk for one of those disorders, have an accumulated absenteeism record of ≥33% for the current year, or have a history of psychotic or autistic spectrum disorders, will be excluded from Tier 2.

### Linkage between Tier 1 and Tier 2

The leadership teams and the counselors will manage the SWPBIS program. They will be in charge of identifying, eliminating, or consolidating existing school-wide interventions that could overlap or interfere with the implementation of SWPBIS. Existing behavioral health services for individual students (*e.g.*, wrap-around services) will be maintained because they will not interfere with SWPBIS. The leadership teams in each school will develop all interventions for Tier 1 while receiving C or C + C. A subcommittee within the leadership team composed of a counselor and an administrator will be in charge of identifying and referring children for participation in Tier 2. Following methods used in other studies [81] each teacher will be asked to rank the children in their classroom from least to most difficulty with externalizing behavior or anxiety and then to refer the top three children with externalizing behavior problems and top three children with excessive anxiety for possible participation in Tier 2. Decisions as to the appropriateness of referrals to Tier 2 will be based on data gathered via teacher ratings on the SDQ [78] and a web-based software system [82] for collecting and summarizing office discipline referrals.

### Setting

The SWPBIS project will be implemented in six K–8 public schools in North Philadelphia, PA, a low-income area that has the second highest level of food insecurity in the country [83]. The ethnic makeup of students is approximately 60% Latino, 30% African American, 10% other minority.

### Training and consultation to leadership teams and counselors

The training model assumes that participating school personnel will need initial training during the first year of the project and briefer retraining each subsequent year. Members of the research team will conduct three days of formal initial training and one day of retraining each with members of the leadership team (LT) and counselors. The training will be delivered using procedures employed in dissemination and implementation studies in nontraditional settings (*i.e.*, initial workshop and subsequent ongoing consultation) [68,84] and other strategies found to be effective according to a recent meta analysis (*i.e.*, active learning strategies) [85].

### External coaches

The support conditions (C, C + C) were modeled after procedures developed by John Lochman and colleagues for the training of school counselors in the context of a dissemination study with the Coping Power Program [68] and recommendations from a recent meta analysis [85]. Consultation will be provided by ‘coaches’ who will be advanced trainees (*e.g.*, interns, fellows) in applied psychology. After initial training, which will be the same for C and C + C, the Tier 1C + C Coaches will conduct one-hour biweekly on-site consultation with members of the LT to help them develop and implement universal interventions throughout the school as delineated in the SWPBIS Team Training Manual [86]. Progress toward the completion of each step in the SWPBIS Team Training Manual will be assessed monthly via the Team Implementation Checklist (TIC) and PBIS Action Plan [87] completed by members of the LT and reviewed by the Tier 1 Coach. In addition, the Tier 1 Coaches will be available to the head of the LT for scheduled one-on-one performance feedback and as needed one-on-one consultation (via telephone or email) about implementation barriers (Individualized Problem Solving). The Tier 1C Coaches will supply the LT an online guide containing steps for the development and implementation of universal interventions. Also, the Tier 1C Coaches will have one-hour biweekly monthly phone conferences with the head of the LT in which progress in completing the steps needed for the development and implementation of interventions as measured via the TIC and PBIS Action Plan will be discussed.

After the initial training related to Tier 2 interventions, which will be the same for C and C + C counselors, the Tier 2C + C Coaches will conduct 14, two-hour weekly on-site consultation sessions with counselors to debrief previous CPP and FRIENDS sessions, observe child group sessions, prepare for upcoming sessions, and conduct problem solving concerning barriers and challenges in the implementation of the protocols. Counselors will receive video-recorded samples of effective implementation of the main components of the treatments (*e.g.*, exposure for anxiety). Tier 2C + C Coaches will also provide individual performance feedback to the counselors after the session is over and will be available to counselors as needed (via telephone or email) for one-on-one consultation about implementation barriers (Individualized Problem Solving). Tier 2C Coaches will conduct two-hour weekly consultation sessions using the same group content and format and they will provide counselors video-recorded samples of effective implementation of the main components of the treatments. However, they will not observe group sessions or offer individualized feedback or individualized support to counselors.

### School recruitment

Upon receiving funding, a presentation of the project was conducted with a preselected group of school administrators from schools in the regional area of interest. Presentations were conducted in person and via GoToMeeting. Those who expressed interest in taking part in the project were asked to respond to a brief request for proposals (RFP). The six schools that applied met the minimal inclusion criteria, so the search was discontinued at this stage. The inclusion criteria included: grade level (any elementary or middle school combination); students’ socio-economic status (percentage of students eligible for free/subsided lunch set at ≥ 90%); racial/ethnic diversity (majority of students are of minority status); and school-wide initiatives (absence of current mental health prevention initiatives). A more in-depth description of the project was provided during staff meetings and a vote was taken. At least 80% of school staff in attendance was required to vote affirmatively in order for the school to join the project. This is a standard cut-off in SWPBIS [88]. Subsequently, the investigators trained members of the leadership teams. As of this writing, the leadership teams are developing interventions for Tier 1 while receiving C or C + C.

### Measures

We employ two measures to help us determine the readiness of school personnel for implementing Tier 1 and Tier 2 interventions. Members of the leadership teams will complete a 23-item checklist [87] to assess completion of activities related to critical features of the SWPBIS model, including regular meetings of the LT and the use of discipline data (*e.g.*, events, dates and time, student, in and out of school suspensions) for program planning and to monitor the schools’ progress in implementing their SWPBIS Action Plan [48]. Members of the leadership teams will complete the instrument monthly; it will also be used by the External Coach to guide members of the LT in developing and implementing Tier 1 interventions in their school.

For Tier 2, following the initial workshop, trainers will assess whether counselors have learned the theoretical underpinnings of CBT and the treatment of anxiety and depression in children. We will use a questionnaire [89] developed for the assessment of knowledge of EBIs in the treatment of youth psychopathology. Counselors will complete the questionnaire right after the initial and last workshop. Counselors scoring below the 80% cutoff will be provided further individual training in the areas in which they scored low.

### Screening, demographics, service utilization

Counselors will ask teachers to complete the SDQ, a mental health screening questionnaire [78,90,91], for children who accumulate ≥3 ODRs or who are referred by a subcommittee of the LT charged with monitoring at-risk children. Children who score ≥1 SD [92] on the Conduct Problems or Emotional Symptoms scales will be invited to participate in a thorough diagnostic assessment.

### Implementation outcome measures

#### Fidelity

Delivering content as originally intended by the treatment developers (content fidelity) leads to better outcomes [93]. Also, delivering content while actively engaging clients in therapy and doing it with a sense of competence (process fidelity) leads to better adherence and outcomes [94-97]. A group of 20 randomly selected teachers, other school personnel and students will be interviewed at the end of each project year in order to assess content fidelity for Tier 1 [98]. Data sources are direct observations, review of school policies and interviews with school staff and students [99]. A cut-off score of 80% on the measure will be used for determining successful implementation of SWPBIS [98].

A checklist reflecting each activity component of the session agenda or outline for CPP and FRIENDS will be used to assess content fidelity for Tier 2. All treatment sessions will be video recorded. Independent coders (ICs) will use a yes-no response scale to indicate whether or not a counselor covered a particular component. Two ICs will complete the checklist after observing video recorded sessions. Differences of within 5% between the 2 ICs will be considered an agreement. We will report the average score between the two ICs.

Our process fidelity checklist is based on a 12-item measure developed by John Lochman and colleagues (*e.g.*, Counselor’s tone is warm and positive). We will use the total score (Overall Process Fidelity) [68]. Twenty percent of sessions one, two, three, and four will be coded, while 30% of sessions five through 14 will be coded by 2 ICs. Differences of within one point between the two ICs will be considered an agreement. We will report the average score between the two ICs.

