### Data analytic plan

The statistical analyses for each of the study aims are described below: in addressing aim one, mean fidelity and its 95% confidence intervals for Tier 1 will be calculated using 20 randomly selected participants from each of the six schools during years three, four, and five (120 total per year). The 95% confidence intervals will be presented by C & C + C for all schools combined and for each school. Content and process fidelity data for Tier 2 will be obtained by scoring 14 video recorded sessions per each of the treatment groups. Perception of School Climate (aim two) during year one will be surveyed by a randomly selected sample of teachers, support staff and administrators from each participant school. The randomly selected sample will consist of similar proportion of teachers, support staff and administrators within each school. The questionnaire [101] will be completed at the end of years one, two, three, four, and five. This 31-item, 5-point Likert type scale checklist has four factors. Each factor’s total score will be analyzed separately. School personnel no longer present in the school during subsequent years will be replaced.

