As an example, the cost-effectiveness ratio for fidelity will reveal how much it costs (or how much it saves) to increase fidelity among the study population by one point. Confidence intervals will be constructed to determine the probability that the difference between two ratios indicates significant differences in cost-effectiveness for the target population. The ratios can then be ordered from lowest to highest to show which intervention is the most cost-effective for increasing the SET score. Administrators then have the information they need to determine if gains in fidelity are sufficient to justify marginal costs. In a similar manner cost-effectiveness ratios can be constructed for other targeted outcomes (*e.g.*, measures of school climate, child symptomatology, impairment, coping skills, symptom severity, and functioning) for comparisons in which the results indicate significant improvement in the intervention group as compared to the control condition.

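### The Fidelity section and the Data analytic plan do not agree on the unit of Tier 1 fidelity: one three-source score per school, or a mean over 20 people per school

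*Protocol article*

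**What the plan says.** Three places in the protocol article bear on Tier 1 fidelity.

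- **Implementation outcome measures, Fidelity.** Interviews are planned: "A group of 20 randomly selected teachers, other school personnel and students will be interviewed at the end of each project year", for the purpose of assessing content fidelity. The next sentence gives the inputs: "Data sources are direct observations, review of school policies and interviews with school staff and students". The success rule follows: "A cut-off score of 80% on the measure will be used for determining successful implementation of SWPBIS".
- **Data analytic plan.** For the first aim, the calculation is stated thus: "mean fidelity and its 95% confidence intervals for Tier 1 will be calculated using 20 randomly selected participants from each of the six schools". It covers years three, four and five, with a yearly total of 120. On reporting: "The 95% confidence intervals will be presented by C & C + C for all schools combined and for each school".
- **Aim four: cost analysis.** The worked example costs a one-point gain in fidelity, then ranks interventions by which is "most cost-effective for increasing the SET score". The article does not spell out SET, but the example uses it as the fidelity score.

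**The concern.** The Fidelity section treats Tier 1 fidelity as a score for a school, with interviews as one of three inputs. The Data analytic plan treats it as something with 20 values in each school, from which a mean and an interval can be formed. A policy review or a direct observation does not naturally yield a separate value for each interviewee, so the two descriptions do not point to the same quantity.

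Fidelity by level of support is the first study aim, and fidelity is also an effectiveness measure in the cost analysis. If the aim-one summary, the 80% success call and the cost per point rest on different scores under one name, they cannot be read together. A school could meet 80% on the measure and sit below 80% on the mean reported for it, or the reverse.

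**Working it through.** **1. The plan's own figure.** Six schools × 20 participants = 120 per year, or 3 × 20 = 60 per arm. This matches the stated 120, so the n counts people and not school scores.

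**2. What each reading implies.**

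| | Mean over interviewees | Three-source total |
|---|---|---|
| Values per school and year | 20 | 1 |
| Values per arm and year | 60 | 3 |
| Values per year | 120 | 6 |
| Place for observation and policy review | none stated | built in |
| On the scale of the 80% cut-off | no | yes |
| 95% CI for one school | can be formed | cannot be formed between units (n = 1) |

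No column satisfies both sections. The stated n and the per-school interval fit only the first; the three sources and the cut-off fit only the second.

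**3. What happens to the intervals.** The half-width of a t-based 95% CI, in SD units, is t(0.975, n − 1)/√n.

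- One school, 20 people: 0.47 person-level SD.
- One arm, 60 people: 0.26 person-level SD.
- One arm, 3 school totals (2 df): 4.303/√3 = 2.48 between-school SDs.

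The SDs differ in kind, so the first two figures cannot be set directly against the third. The point is that the choice of unit decides which interval exists.

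Even on the interviewee reading, an arm interval that counts 60 independent people ignores the three randomized schools. With an assumed intraclass correlation of 0.01 to 0.20, the design effect 1 + 19 × ICC runs from 1.19 to 4.80. An interval on 2 df would then be (4.303/2.001) × √(design effect) = about 2.3 to 4.7 times as wide.

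**4. Can the choice of score change the 80% verdict?** Let w be the interview share of the total, I the interview part and O the observation and policy part. Total = w·I + (1 − w)·O, and it differs from the interview figure by (1 − w)(O − I). The article gives none of w, I or O; every value below is assumed.

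| w | Total if I = 70, O = 90 | Total if I = 90, O = 70 |
|---|---|---|
| 0.25 | 85.0 | 75.0 |
| 1/3 | 83.3 | 76.7 |
| 0.50 | 80.0 | 80.0 |
| 0.75 | 75.0 | 85.0 |

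The interview figure alone fails in the first case (70) and passes in the second (90). Counting 80 as a pass, the verdict on the total is different at w of 1/3 or less in both cases, and at 0.50 in the first case only. At 0.75 it is the same in both. So a change of verdict is possible in either direction, but not inevitable.

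**The case against.** The best defence is that the Data analytic plan is only brief. Its 20 participants are evidently those interviewed under Fidelity, where interviews are listed as one input among three, so the phrase may simply point back to the full measure. How the instrument combines its sources rests on cited references that are not at hand, and an article may leave score assembly to the full protocol. The cost section moves from fidelity to SET within one example, which suggests that the authors have a single instrument in mind.

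Much of this stands, and it rules out stronger readings:

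- A reader might infer that the plan drops observation and policy review. It does not say so; it only leaves them without a stated place.
- A reader might infer that the plan judges the interviewee mean against 80%. The Data analytic plan does not mention the cut-off, and the Fidelity section applies it to the measure.
- A reader might infer that the mix of teachers, other personnel and students biases the figure. The 20 are drawn at random, so variation in who is drawn is ordinary sampling variation.
- A reader might infer that a gain in one arm would be understated. Nothing in the article shows how the arms would differ across the sources.

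The defence does not remove the conflict. The analysis section fixes an n of 120 and an interval for each school. If the 20 are only an input to a full score, both are wrong as written. An unseen plan could resolve this only by departing from one of the two sections, so it is more than omitted detail.

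**Conclusion.** The point holds as an inconsistency about the unit of Tier 1 fidelity. Either the reported mean is interview-based and is not on the scale of the 80% cut-off, or it is the three-source score and the stated n and per-school interval must go.

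The argument rests on one assumption about an instrument that is not shown: that observation and policy review are scored for the school and not once per interviewee. The size of any gap between the two scores cannot be computed from the article, and the tabulated values only show that the choice can matter. The inconsistency should be settled before the aim-one analysis, because the same score feeds aim four.

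**What to change.** In the Data analytic plan, define Tier 1 fidelity as the measure's total score for each school and year, assembled from all three sources as the instrument prescribes, with the 20 interviews as one input. Apply the 80% cut-off to that total. Use it for the aim-one summary by arm and for the fidelity ratio under Aim four, and say there that it is the SET score.

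The sentence promising intervals must change with it. Report each school's total without a between-person interval, and base any arm-level interval on the schools, three per arm. Interviewee-level results may be shown as description only.

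No new data are needed, since all three sources are already planned. The price is precision on paper: six scores a year in place of 120 records, no interval for a single school, and wide arm intervals on 2 df per arm.

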#### Process evaluation

We will conduct focus groups with members of the leadership teams and other school personnel at the end of each project year in order to assess perceptions of the appropriateness of C and C + C level of support for the implementation of SWPBIS.

#### Children’s functioning

We will collect children’s academic performance, absenteeism, and office discipline referrals (ODR) throughout the five years of the project. Absenteeism data will be collected from the school’s daily attendance records. Academic performance will be taken from the state’s mandatory testing for reading and math for all students. ODRs will be collected using a web-based system for monitoring ODRs to assist in intervention planning and evaluation [100]. These data will be used for determining inclusion into Tier 2 and to measure outcomes. We will also record in- and out-of-school suspensions per 100 students per year and percentage of students receiving suspensions. These indices are reliable and valid for measuring intervention effects [82].

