## Methods/Design

Six K–8 schools in the School District of Philadelphia were randomly assigned to either Consultation or Consultation plus Coaching (See Figure 2). A stratified random assignment list of schools to condition was generated using a computerized random assignment program [77]. Schools were stratified to group one if their baseline School Climate (CREST) scores were below the median CREST scores or to group two if the CREST scores ≥ the median value. The units of analyses for Tier 1 are all of the students in those K-8 schools (650 per school), leadership team members (eight per school) and other school staff (30 per school). The units of analyses for Tier 2 are the children meeting criteria for inclusion in one of the GCBT groups (enroll a total of 367 students assuming a 17% dropout; approximately 51 eligible students per school), the school counselors (two per school) conducting the GCBT groups, and the groups themselves (14 per school; see Table 1).

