The general analytical approach for testing our hypotheses will be the Laird and Ware mixed effects model [112] and the Generalized Estimating Equation (GEE) approaches [113,114]. Mixed effects and GEE are statistical approaches based on regression techniques for analyzing correlated data collected repeatedly from the same subject. The study design will allow us to examine the between- subjects effect related to the two levels of support, and a within-subjects effect corresponding to time points (five time points), as well as a type of support (C, C + C) by time interaction effect. These analyses will be conducted using SAS Proc Mixed, which utilizes the mixed effects models, and SAS Proc Genmod, which utilizes GEE [115]. Both the mixed effects model and GEE approaches allow estimation of fixed effect parameters such as time, and time by treatment interaction. If the interaction term is significant, it indicates that change in school climate and/or reduction in ODRs over time is significantly different between the two levels of support. If the interaction term is statistically not significant, the changes over time for the two primary outcomes will be presented by the time effect only, which represents both levels of support. The advantage of utilizing these methods is that all information available from each student is used, including variables with missing observations. In the proposed analyses, we will consider students measured within classes are correlated and will be nested within classes. Nested analysis will be chosen as part of Proc Mixed and Proc GEE, as such, the intraclass ‘intracluster’ correlation (ICC) will be part of the overall variance covariance matrix.

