Changes from pre- to post- implementation in diagnostic status, symptom severity and impairment level, coping skills and academic productivity during Implementation across all schools, regardless of level of support, will be analyzed using McNemar tests. For each of the listed primary outcomes, a series of 2X2 tables will be constructed to test changes from pre- to post- in the pertinent categories using McNemar tests. Alpha level will be adjusted to 0.025 based on Bonferroni criteria for multiple comparisons. We will also use McNemar tests to test the hypothesis that the pre- to post- level of improvement in diagnostic status, symptom severity, impairment level, coping, and academic productivity obtained during Implementation will be maintained during Sustainability among schools receiving C + C.

We would like to determine whether pre- to post- improvement in diagnostic status, symptom severity, impairment level, and academic productivity differ by support condition during the implementation phase. In addressing this research question, and for the sake of simplifying the statistical analysis, each student will be categorized as either improved or not improved based on change from pre- to post-. A category one will be assigned if a student’s diagnostic status, for example, changes either from positive to intermediate, intermediate to negative, or positive to negative. Otherwise a score of zero will be assigned. Similar coding will be used for symptom severity, coping, impairment level, and academic productivity. We will use chi-squared tests to compare the proportion of (yes/no) for each of the primary outcomes between C and C + C type of supports. To examine changes in the rate of ODRs between baseline and follow up during each school year, the number of students with at least one ODR will be defined at baseline and at the follow up and a 95% confidence interval for such changes will be constructed for each of the five years.

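### The C versus C + C test of child improvement ignores entry severity, although Tier 2 children are identified after allocation by teams receiving the allocated support

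*Protocol article*

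**What the plan says.** **Order of events.** Methods/Design reports allocation as done: "Six K–8 schools in the School District of Philadelphia were randomly assigned to either Consultation or Consultation plus Coaching". School recruitment adds: "As of this writing, the leadership teams are developing interventions for Tier 1 while receiving C or C + C". Tier 2 identification is described throughout as still to come.

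**Who identifies the children.** Under Linkage between Tier 1 and Tier 2, a subcommittee of the leadership team "composed of a counselor and an administrator will be in charge of identifying and referring children for participation in Tier 2". Teachers rank their class and refer the three children with the most externalizing difficulty and the three with the most anxiety. Whether a referral is appropriate is judged on the teacher SDQ and ODR records. Under Screening, demographics, service utilization, teachers complete the SDQ "for children who accumulate ≥3 ODRs or who are referred by a subcommittee of the LT charged with monitoring at-risk children".

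**Role of ODRs.** Children's functioning says of the ODR data: "These data will be used for determining inclusion into Tier 2 and to measure outcomes". The Data analytic plan tests whether "change in school climate and/or reduction in ODRs over time is significantly different between the two levels of support".

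**Entry criteria, the same in both arms.** Inclusion criteria require an SDQ score at or above 1 SD. They also require a primary diagnosis of ODD, CD, GAD, SAD or SP at Intermediate or Positive level, from a parent structured interview and a severity scale completed by an independent rater.

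**The comparison between arms.** The Data analytic plan codes each child as improved or not from pre to post, then states: "We will use chi-squared tests to compare the proportion of (yes/no) for each of the primary outcomes". No baseline covariate or stratum is named.

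**The concern.** Randomising schools balances, in expectation, what exists at the time of allocation. It does not balance a sample of children that forms afterwards and whose formation the allocated support may influence.

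Here the people who identify children belong to the teams being supported, and one of their data sources is a measure that the support is meant to change. The Interventions section expects Tier 1 to reduce the number of children who develop externalizing or anxiety problems, so a difference between arms in Tier 1 success would itself alter the pool from which Tier 2 is drawn. The effect could go either way. Better-supported teams might find more mild cases, or might leave a smaller and more severe group to refer.

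If the enrolled children differ in severity between arms, an unadjusted test of improvement mixes the effect of coaching with the effect of case mix.

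**Working it through.** The plan gives no figure for case mix, so there is none to reproduce. The check has two parts.

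**1. Does the outcome coding depend on entry level?** Eligible children enter at Intermediate or Positive. Under the Data analytic plan a child counts as improved in diagnostic status as follows:

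- entry Positive: moves to Intermediate, or to Negative (two routes);
- entry Intermediate: moves to Negative (one route).

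The chance of being coded improved can therefore differ by entry level. Coding each child's own change does not adjust for where the child started.

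**2. How far could this move the chi-squared test?** Input from the documents: 153 evaluable children per arm (Table 1). Assumed: no true support effect, two-sided 5% level, clustering ignored, a Positive share *s* in each arm, and improvement rates *p*P (Positive) and *p*I (Intermediate).

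Expected proportion improved in an arm: *s*·*p*P + (1 − *s*)·*p*I.

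With *p*P = 0.50 and *p*I = 0.30:

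- arm with *s* = 0.60: 0.60 × 0.50 + 0.40 × 0.30 = 0.42
- arm with *s* = 0.40: 0.40 × 0.50 + 0.60 × 0.30 = 0.38
- spurious difference: 0.42 − 0.38 = 0.04
- pooled SE: √(2 × 0.40 × 0.60 / 153) = 0.0560
- unpooled SE: √((0.42 × 0.58 + 0.38 × 0.62) / 153) = 0.0560
- rejection: Φ[(0.04 − 1.96 × 0.0560)/0.0560] + Φ[(−0.04 − 1.96 × 0.0560)/0.0560] ≈ 0.106 + 0.004 = 0.110

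Range over other assumed inputs (absolute difference; rejection rate):

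| Improve: Positive / Intermediate | Shares 55% v 45% | Shares 60% v 40% | Shares 70% v 30% |
|---|---|---|---|
| 50% / 40% | 1 point; 5.4% | 2 points; 6.4% | 4 points; 10.8% |
| 50% / 30% | 2 points; 6.5% | 4 points; 11.0% | 8 points; 29.7% |
| 60% / 30% | 3 points; 8.2% | 6 points; 18.4% | 12 points; 56.0% |
| 30% / 50% | 2 points; 6.5% | 4 points; 11.0% | 8 points; 29.7% |

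In the last row the severity gradient is reversed, and the spurious difference changes sign. With equal shares the rejection rate is 5%.

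**Effect of using the baseline level.** The unadjusted test and a Mantel-Haenszel test stratified on baseline diagnostic level were simulated, 20,000 runs per scenario:

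| Improve: Positive / Intermediate | Shares | Unadjusted | Stratified |
|---|---|---|---|
| 50% / 30% | 50% v 50% | 5.2% | 4.9% |
| 50% / 30% | 60% v 40% | 11.3% | 5.1% |
| 50% / 30% | 70% v 30% | 30.7% | 4.7% |
| 60% / 30% | 60% v 40% | 17.7% | 4.8% |
| 60% / 30% | 70% v 30% | 56.1% | 5.0% |

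The stratified test performs this well because the imbalance was placed wholly in a measured variable. It would not correct a difference in something unrecorded.

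**The case against.** **The safeguards are real.** Three ODRs only prompt a teacher SDQ, and no child enters on ODR count alone. Entry then needs the common SDQ cut-off and a diagnosis from a parent interview and an independent rater. The top-three ranking is the same rule in every classroom. This stands, and it narrows the room for imbalance. It does not close it. The criteria act only on children already referred, a ranking within a class fixes relative rather than absolute severity, the SDQ is completed by a teacher in the allocated school, and two diagnostic levels qualify.

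**The plan has other models.** The mixed-model and GEE approach and the nested analysis in the Discussion address repeated measures and clustering. Neither is described as adjusting for case mix, and for this question the chi-squared test is the one named. It is a stated choice, not a detail left to a fuller document.

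**The size is speculative.** This also stands. Nothing in the documents supports a particular imbalance, and the 70% v 30% column in particular marks an extreme, not a forecast.

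**A stronger reading to avoid.** From the dual use of ODRs a reader might infer that ODRs will fall by selection alone in children picked for high counts, and that the ODR analysis must be moved to the whole school. The documents do not support this. ODRs are not among the Tier 2 outcomes compared by chi-squared. They go to the support-by-time model and to yearly counts of students with at least one ODR, and Methods/Design sets the Tier 1 unit as all students. Nor is the absence of a flow table by arm a defect in an article of this kind.

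**Conclusion.** The point holds as a weakness in the analysis of the Tier 2 child outcomes. Children are identified after allocation, by teams receiving the allocated support and partly from data that the support is meant to change. The named comparison of C with C + C takes no account of entry severity, and its outcome coding is sensitive to it.

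The contrast can be biased. The documents do not show that it will be, by how much, or in which direction. On the assumptions above, a 60% v 40% difference in the Positive share with improvement rates of 50% and 30% yields 4 points and about 11% rejection in place of 5%. Across the assumed range the figures run from 1 to 12 points and from about 5% to 56%. The case for change rests less on these figures than on the ease of the remedy.

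**What to change.** In the Data analytic plan, replace the chi-squared comparison of improved versus not improved between C and C + C with a model of the post-treatment outcome on arm:

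- logistic or ordinal for diagnostic status, linear for scale scores;
- adjusted for the child's own baseline level of that outcome and for primary diagnosis group (externalizing or anxiety);
- with school as the cluster.

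State that adjustment corrects measured imbalance only. With three schools per arm, the school term rests on few clusters, a limit that the Discussion already acknowledges in general terms.

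The cost is a change of wording. Diagnostic status, symptoms, coping, impairment and academic productivity are already collected before and after treatment, and primary diagnosis is established at entry. Entry rules, the planned ODR analyses and the sample size are untouched.
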